### 1.3 Planned sample size

This pilot study will include 120 randomized patients, which, accounting for randomized but untreated patients and patients who withdraw in both arms, is expected to provide at least 100 evaluable patients, with 50 in each arm. This population size is expected to be sufficient to allow selection of an appropriate clinical endpoint for the confirmative Phase 3 study and to determine feasibility. No statistical sample size estimation has been involved.

|                           |                 |             |              |
|---------------------------|-----------------|-------------|--------------|
| Statistical Analysis Plan | Version 2.0     |             | Page 8 of 19 |
| Sponsor                   | [name] | Protocol No | FARES        |

## 2 GENERAL INFORMATION

### 2.1 Background details

All study data will be transferred to a SAS database (version 9.4 or later) for statistical analysis purposes. Data will be imported from an Electronic Data Capture System (OPVerdi) via validated SAS programs. If applicable, external data will also be transferred to SAS for presentation of these data in the statistical analyses.

The SAP will be finalized before any unblinded analysis after agreement with the Sponsor.

### 2.2 Deviations from the trial protocol with regard to statistical analyses

Overall, there were no deviations from the statistical methods stated in the protocol. However, to closer study attributable efficacy and safety results, additional exploratory analyses have been added, focusing explicitly on additional time windows. The additional time windows for these exploratory analyses are identified with italic font in section 5 below.

### 2.3 Individual protocol deviations

No specific protocol deviations will be considered as this is a non-interventional, pragmatic study.

A detailed review of all documented and derived deviations from protocol will be part of the Data Review Meeting (DMR) before database lock. During this DRM the impact of protocol deviations on the analysis will be assessed and the conclusions documented.

A complete listing of protocol deviations (documented as well as derived ones) and the judgment for assessment of subject disposition will be signed before clinical database lock. A description of protocol violations that led to exclusion from any analysis sets will be included in the table part of the Clinical Study Report (CSR).

## 3 ANALYSIS POPULATIONS

Due to the emergency nature of the condition being studied the trial will include only patients who are incapable of providing informed consent at the time the therapy is needed and in whom delays in obtaining surrogate consent can be severely detrimental to their well-being. Thus, this study qualifies for alteration to consent requirement before randomization. Therefore delayed consent from patients or surrogate decision maker (SDM) where appropriate will be sought after surgery.

As a rule, only data from enrolled patients with informed consent will be analyzed.

Data from randomized and treated patients who refused to give consent will be excluded from any analysis.

To ensure that the safety reporting is complete, all hemostatic therapy and severe or life-threatening serious adverse event data will be collected in cases where consent for remaining in the study cannot be obtained.

|                           |                 |             |              |
|---------------------------|-----------------|-------------|--------------|
| Statistical Analysis Plan | Version 2.0     |             | Page 9 of 19 |
| Sponsor                   | [name] | Protocol No | FARES        |

Hence, the disposition of patients will be displayed according to the following analysis populations:

- All Patients Enrolled (APE) population
- Failed Consent Patients (FCP) population
- Safety (SAF) population
- Intention-To-Treat (ITT) population
- Per-Protocol (PP) population

Membership of subjects will be decided upon in a DRM with the Sponsor before database lock. The proper flags for analysis sets exclusion (e.g., exclusion from PP set), will be included in the analysis datasets. The protocol deviation list should be finalized before database lock.

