### 9.2 Statistical Analysis

For the statistical analysis of the efficacy parameters the following analysis populations will be considered:

The statistical analyses will be performed on the intention to treat (ITT) population, which will include all randomized and treated patients who consent to the study. Randomized patients who did not undergo cardiac surgery or received no IMP will be excluded from the analysis. It is anticipated that <20% of patients will fall into these categories. In the event that a patient receives treatment that is not in concordance with the randomization schedule, the treatment group will be defined according to the randomization (rather than the actual treatment received).

The per-protocol (PP) population: This analysis population will consist of all patients in the ITT population, excluding patients with important protocol deviations that may affect the statistical analysis. The following patients will be excluded by default:

- Patients who receive an IMP different to the IMP assigned by randomization
- Patients who receive less than 80% of the planned dose
- Patients who significantly violate inclusion/exclusion criteria

A final decision about the classification of protocol deviations and their consequences regarding assignment of patients to analysis populations will be made during the data review meeting prior to the final analyses. Decisions and outcome will be approved by the Principal Investigator (Sponsor) in consultation with the funder (Octapharma).

The ITT analysis population is considered the primary population for analysis of the efficacy objectives.

Descriptive statistics with 95% confidence intervals will be used to describe the data. Simple tests of comparison will be used to compare outcomes between the two groups. The summary tables and exploratory inferences will be chosen according to the scaling level of the measurements, e.g. frequency tables and Chi-square tests for categorical responses, sampling statistics and F-tests for continuous data.

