### 9.2.1 Safety Analysis Plan

The safety analysis population (SAF) will include all patients who received at least one dose of the IMP who consent to the study (if no randomization errors occur, this will be the same population as the ITT population). Safety outcomes will be analyzed by presenting point estimates and two-sided 95% CIs in addition to descriptive statistics.

To ensure that the safety reporting is complete, all hemostatic therapy and Grades 3 and 4 SAE (as per the FDA criteria: severe or life-threatening) data will be collected in cases where consent for remaining in the study cannot be obtained.

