few days and consent will be obtained from the patient when appropriate. Consent should be obtained within the 28 day duration for each study patient. Any delays in obtaining consent due to extenuating circumstances need to be clearly documented (e.g., a patient dies soon after surgery in which case initiation of consent process from next-of-kin can be delayed for up to 2-weeks after death). Study data collection will begin only after informed consent is obtained from the SDM or patient.

Study coordinator or assistant will obtain freely given consent (in person or via telephone/-) from each patient (or SDM) after an appropriate explanation of the aims, methods, anticipated benefits, potential hazards, and any other aspect of the study which is relevant to the decision to continue to participate. E-mail will be used as a method of correspondence where requested to send the consent form for review. Consent must be obtained by the patient (or SDM), before the patient is exposed to any further study-related procedures, namely evaluation and data collection. Should the consent be obtained from the SDM and later withdrawn by the patient, no additional data will be collected. To ensure that the safety reporting is complete, all hemostatic therapy and Grades 3 and 4 SAE (as per the FDA criteria: severe or life-threatening) data will be collected in cases where consent for remaining in the study cannot be obtained.

Study coordinator or assistant will explain that the patients/SDM are completely free to withdraw from the study at any time, without any consequences to their future care and without the need to justify. Each patient will be informed that his/her medical (source) records may be reviewed by the study monitor, a quality assurance auditor, or a health authority inspector, in accordance with applicable regulations, and that these persons are bound by confidentiality obligations. In addition to the study protocol, study hospitals will also follow their institutional guidelines and approvals when consenting and collecting data. Their process will be documented in their SOPs. Again, no data will be collected on patients/SDMs who refuse consent. Please refer to Appendix in 15.2 for the consent and data collection guidelines at Toronto General Hospital.

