### 3.2 Failed Consent Patients (FCP) Population

The FCP) population will consist of all enrolled patients who received at least one treatment with either PCC or FP for whom consent cannot be obtained. This population will only be used for displays of hemostatic therapy and severe or life-threatening serious adverse events.

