### 3.4 Intention-To-Treat (ITT) Population

The Intention-To-Treat (ITT) population will include all enrolled patients who have given informed consent and who received at least one treatment with either PCC or FP and underwent cardiac surgery. In the event that a patient receives treatment that is not in concordance with the randomization schedule, the treatment group will be defined according to the randomization (rather than the actual treatment received).

|                           |                 |             |               |
|---------------------------|-----------------|-------------|---------------|
| Statistical Analysis Plan | Version 2.0     |             | Page 10 of 19 |
| Sponsor                   | [name] | Protocol No | FARES         |

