## 4 STATISTICAL ANALYSES

All statistical analyses will be performed using the SAS® software (Version 9.4 or later).

The analysis of safety will be based on the SAF and additionally on the ITT population.

The primary evaluation of overall efficacy will be performed on the ITT population. In addition selected efficacy analyses will also be presented for the PP population.

If not stated otherwise the following standard descriptive statistics will be presented:

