## 4.7 Safety

All safety analyses will be based on the ITT population. If the SAF population differs from the ITT population then only AE information will additionally be displayed for the SAF.

The analysis of safety will study the following primary endpoints:

1. All adverse events (AEs) and serious AEs (SAEs) collected from beginning of surgery to postoperative day 28.

|                           |                 |             |               |
|---------------------------|-----------------|-------------|---------------|
| Statistical Analysis Plan | Version 2.0     |             | Page 15 of 19 |
| Sponsor                   | [name] | Protocol No | FARES         |

- a. SAEs collected individually and as a composite (death, myocardial infarction, stroke, acute liver injury, acute kidney injury and thromboembolic events).
- b. Transfusion-Related Acute Lung Injury (TRALI) and Transfusion-Associated Circulatory Overload (TACO)

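### Treated patients whose consent cannot be obtained are left out of every between-arm comparison, their vital status is not expressly secured, and the SAP names two different main safety populations

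*Combined protocol and SAP*

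**What the plan says.** **Who is analysed.** SAP section 3 gives the rule: "As a rule, only data from enrolled patients with informed consent will be analyzed". SAP 3.4 applies it: "The Intention-To-Treat (ITT) population will include all enrolled patients who have given informed consent", with treatment and cardiac surgery as further conditions. Protocol 9.2 defines ITT as "all randomized and treated patients who consent to the study". The safety population (SAF) also requires consent, in SAP 3.3 and in protocol 9.2.1.

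**Where the others go.** Treated patients whose consent cannot be obtained form the FCP population (SAP 3.2): "This population will only be used for displays of hemostatic therapy and severe or life-threatening serious adverse events". The All Patients Enrolled set (SAP 3.1) is used only for disposition.

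**How consent is sought.** Protocol 10.3 has the patient or a surrogate decision maker (SDM) approached 24 to 72 hours after surgery, with repeat visits and consent expected within the 28-day study period. Delays are allowed if documented, for example when "a patient dies soon after surgery in which case initiation of consent process from next-of-kin can be delayed for up to 2-weeks after death".

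**What is collected without consent.** Protocol 9.2.1: "all hemostatic therapy and Grades 3 and 4 SAE (as per the FDA criteria: severe or life-threatening) data will be collected". Protocol 10.3 and Appendix 15.2 repeat the list. Appendix 15.2, written for Toronto General, describes the group as patients with no SDM or lacking capacity. Nothing is collected from those who decline.

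**Which set carries safety.** SAP 4: "The analysis of safety will be based on the SAF and additionally on the ITT population". SAP 4.7: "All safety analyses will be based on the ITT population"; it then limits the SAF display, where SAF differs from ITT, to adverse-event information. Protocol 9.2.1 names SAF as the safety population. SAP 2.2 reports no deviations from the protocol's statistical methods.

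**The concern.** Consent comes after treatment, so membership of ITT and SAF is partly decided by what happened after treatment. A patient who stays incapacitated and has no surrogate cannot enter either set. Lasting incapacity can follow from bleeding, stroke or thrombosis, which the trial measures. Removing such patients from the comparison is selection on a post-treatment state, and randomization does not protect against it.

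Protocol 1.2 says the pilot will feed the Phase 3 sample size and serve to detect early safety problems. Mortality and composite rates based on consenting patients alone could be too low, and a between-arm difference could be shifted if consent failures differ by arm.

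Two further points bear on the same outputs. If the no-consent list does not clearly include death, the separate FCP display may not repair the omission. And if the SAP names two different main safety sets, the programmer must choose between counting patients as treated and counting them as randomized.

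**Working it through.** **1. The only related planning figure.** The plan randomizes 120 to obtain at least 100 evaluable patients, 50 per arm (protocol 9.1, SAP 1.3), and says no statistical calculation was made.
- Loss implied by 120: (120 − 100)/120 = 16.7%.
- At the 20% bound in protocol 3.3.8: 100/(1 − 0.20) = 125 would be needed, and 120 × 0.80 = 96 would remain.

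So 120 fits a loss of up to 16.7%. Protocol 3.3.8 pools three reasons for loss (untreated, no index procedure, no consent) and expects most to be untreated. Untreated patients are not FCP. The bound caps all losses at fewer than 0.20 × 120 = 24 patients, and the FCP share of these cannot be derived.

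**2. An FCP patient traced through the outputs.**

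| Output | Set used | FCP patient included? |
|---|---|---|
| P1 to P3 (SAP 4.6) | ITT, also PP | No |
| Safety composite (SAP 4.7) | ITT, AE information also on SAF | No |
| Mortality risk ratio, Kaplan-Meier (SAP 4.7.1) | as above | No |
| Hemostatic therapy, severe or life-threatening SAEs (SAP 3.2) | FCP | Display only |

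No planned comparison includes the patient.

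**3. What could be derived for FCP patients.**
- Hemostatic agents, platelets and a second dose of study product: covered by the hemostatic-therapy item.
- Red cells: probably covered, but to be confirmed. Protocol 7.2.2 lists blood products and then other hemostatic agents, yet also names the two categories separately.
- Surgical re-exploration (part of P1): not clearly covered.
- Composite events below Grade 3: not covered.
- Death: not named. Protocol 7.4.3 lists death and life-threatening events as separate seriousness criteria, and says some SAEs expected from the surgery will not count as SAEs. Protocol 7.4.2 treats death as an outcome of an event, with the causing event to be fully reported. A fatal event may therefore enter with a fatal outcome, but the list does not guarantee vital status.

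**4. Size, illustration only.** One death in 50 is 1/50 = 2.0 percentage points. Assume 50 consenting patients and 2 deaths per arm, plus *k* FCP patients per arm. None of these death or FCP counts is in the documents.
- Arm mortality ranges from 2/(50 + k) if no FCP patient dies to (2 + k)/(50 + k) if all die.
- If the FCP deaths all fall in one arm, the risk ratio is (2 + k)/2 or its inverse.
- 95% CI: exp[ln RR ± 1.96 × √(1/a − 1/n₁ + 1/b − 1/n₂)], with *a*, *b* the deaths and n₁, n₂ the arm sizes.

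| k per arm | Arm mortality, none to all die | Risk ratio, FCP deaths all in one arm (95% CI) |
|---|---|---|
| 0 | 4.0% | 1.00 (0.15–6.82) |
| 1 | 3.9% to 5.9% | 0.67 (0.12–3.82) or 1.50 (0.26–8.60) |
| 2 | 3.8% to 7.7% | 0.50 (0.10–2.61) or 2.00 (0.38–10.45) |
| 5 | 3.6% to 12.7% | 0.29 (0.06–1.31) or 3.50 (0.76–16.11) |

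With 3 deaths per arm instead, the risk ratios span 0.75–1.33, 0.60–1.67 and 0.38–2.67. The point estimate moves, but every interval stays wide and includes 1.

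**5. The safety set.** SAP 4 puts SAF first; SAP 4.7 puts ITT first. SAF groups patients by treatment received and does not require cardiac surgery; ITT groups them as randomized and does. Laboratory data have their own section (SAP 4.7.2), outside adverse events, so under SAP 4.7 they would be shown only as randomized. The mortality text sits inside the adverse-event section (SAP 4.7.1), so it can be read as repeated on SAF.

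**The case against.** The plan has real safeguards. Surrogate consent, repeat visits and approach to next of kin after a death keep many severely ill patients in the analysis. Death does not by itself make a patient FCP; the group at risk is those for whom neither the patient nor anyone on the patient's behalf can consent. FCP is prespecified and displayed, and the SAP appendix requires every subject listing to show arm and analysis set. The study is an exploratory pilot with no confirmatory test. Protocol 9.2.1 expects SAF and ITT to coincide if there are no randomization errors. All of this stands, and it limits the consequence.

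Four stronger readings are tempting, and the documents do not support them:
- *The sickest patients drop out.* This is inference. The consent routes above work against it, and neither the number of FCP patients nor their outcomes are given.
- *Deaths are not collected.* The list does not name death, but a fatal event may enter as a severe or life-threatening SAE with a fatal outcome. The text is ambiguous; a data gap is not proven.
- *Everything needed is already collected, so P1 to P3 and the composite could be rebuilt.* Re-exploration and composite events below Grade 3 may be missing. A full reanalysis including FCP would undercount events in that group.
- *Mortality is never shown as treated.* Its place in SAP 4.7.1 allows an SAF display. Only laboratory data are clearly limited to ITT.

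The safeguards do not remove the exclusion itself: no comparison, even as a sensitivity analysis, includes these patients.

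**Conclusion.** The point holds in a limited form. Treated patients whose consent cannot be obtained are absent from every between-arm comparison, and inclusion depends partly on a state that arises after treatment. This can bias the mortality and safety estimates passed to Phase 3. Neither the size nor the direction between arms can be established from the documents. The figure of about 2 percentage points per omitted death rests only on the planned 50 per arm; the risk-ratio shifts rest on assumed death and FCP counts. The no-consent list leaves vital status unsecured.

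The conflict between SAP 4 and SAP 4.7 needs no assumption. SAP 4.7 also departs from protocol 9.2.1, despite the statement in SAP 2.2. Its practical effect is confined to patients given the wrong product and treated patients without cardiac surgery, who may be few.

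This is a worthwhile, inexpensive correction for an exploratory pilot, not a flaw that invalidates it. The safety set should be settled before the outputs are programmed.

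**What to change.** 1. **Align SAP 4.7 with SAP 4 and protocol 9.2.1.** Make SAF, as treated, primary for all safety outputs, stating explicitly that this includes mortality and laboratory data, with ITT supportive.
2. **Bring FCP into view by arm.** Report the number of FCP patients, their severe or life-threatening SAEs and their known deaths by arm. Add sensitivity analyses of mortality in SAF plus FCP, and, in ITT plus FCP, of those transfusion and hemostatic-agent endpoints that the collected data allow. State that re-exploration and composite events below Grade 3 may be missing. Patients who declined stay excluded.
3. **Name death (vital status) in the no-consent list** in protocol 9.2.1, protocol 10.3 and Appendix 15.2, subject to research ethics board (REB) approval.

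Items 1 and 2 cost SAP wording and a few tables, and do not wait on item 3. Item 3 needs an amendment submitted under protocol 10.4. Because SAP version 2.0 followed the blinded data review meeting, it may also mean going back to charts, within the consent limits the protocol sets. The remaining drawback is incomplete endpoint data in FCP, which is why these analyses should be sensitivity analyses and not replace the main ones.

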### 3.1 All Patients Enrolled (APE) Population

The APE population will include all enrolled patients regardless of the consent status who received at least one treatment with either PCC or FP. This population will only be used for displays of subject disposition.

### 3.2 Failed Consent Patients (FCP) Population

The FCP) population will consist of all enrolled patients who received at least one treatment with either PCC or FP for whom consent cannot be obtained. This population will only be used for displays of hemostatic therapy and severe or life-threatening serious adverse events.

### 3.3 Safety (SAF) Population

The Safety (SAF) population will include all enrolled patients who have given informed consent and who received at least one treatment with either PCC or FP regardless whether they underwent cardiac surgery or not. In the event that a patient receives treatment that is not in concordance with the randomization schedule, the treatment group will be defined according to the actual treatment received.

### 3.4 Intention-To-Treat (ITT) Population

The Intention-To-Treat (ITT) population will include all enrolled patients who have given informed consent and who received at least one treatment with either PCC or FP and underwent cardiac surgery. In the event that a patient receives treatment that is not in concordance with the randomization schedule, the treatment group will be defined according to the randomization (rather than the actual treatment received).

|                           |                 |             |               |
|---------------------------|-----------------|-------------|---------------|
| Statistical Analysis Plan | Version 2.0     |             | Page 10 of 19 |
| Sponsor                   | [name] | Protocol No | FARES         |

